### Quality control and monitoring

Several strategies will be implemented to ensure quality control of the data and intervention. The introductory sessions will be standardised to ensure consistency between sites and between instructors. Assessors will be trained on the tasks with videos and will complete mock testing sessions that will be used to assess adherence to the protocol. Regular controls will be done regarding recruitment and assessment by site coordinators. Any modification to the protocol will be shared with the investigators and among sites and reported to the ethics committee. Internal audits will be conducted to ensure the proper conduct of the study and to certify that it complies with the protocol. Shortly after the beginning of the study and again once the study is completed, data from five participants will be selected randomly and verified by a researcher not involved in data collection. This person will ensure that informed consents have been signed, that eligibility criteria have been respected, and that all the tests relative to the assessments have been properly completed and original documents scanned and uploaded in REDCap.

### Potential harms

Falls are one of the adverse events that could occur during the study. Participants will be asked to report the occurrence of a fall and its severity in the last year for T0, and in the T0-T1 and T1-T2 periods [79]. In addition, participants will be asked to report and discuss any potential adverse event during home visits and phone calls. These will be classified according to the typology developed in [80]: falls that require medical attention; exacerbation of a pre-existing illness; increase in the frequency or intensity of a pre-existing episodic event or condition; condition detected or diagnosed after the intervention, even though it may have been present prior to the start of the study; continuous persistent disease or symptoms present at T0 that worsened following the start of the study. All adverse events will be assessed for severity, expectedness and causality and will be recorded and closely monitored until resolution or stabilisation or until it is shown that the study intervention was not the cause.

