## Objectives and hypotheses

The StayFitLonger study has two major objectives that will be addressed in the trial and the sub study. The **efficacy trial** will test the effect of the training on physical, cognitive, affective, and psychosocial outcomes using a 26-week double-blind parallel-group randomised control trial (RCT). Participants will be allocated randomly to either the StayFitLonger training home-based computerised programme (experimental intervention) or a home-based computerised comparator (active control). The primary objective is to assess whether the StayFitLonger programme leads to larger pre-post improvement than the active control condition on the Timed-Up & Go (TUG), a broadly used and validated functional physical task to measure lower extremity function, mobility and balance. Participants allocated to the experimental intervention are expected to show larger post-training improvement on the TUG than participants in the control intervention. As a secondary objective, we will assess whether the StayFitLonger programme improves physical, cognitive, affective, and psychosocial secondary outcomes. We will also explore whether gains differs in robust vs. pre-frail seniors since some studies suggest that changes in response to training might depend on frailty status [11, 14].

The **adherence sub-study** will rely on a pragmatic quasi-experimental design. At the end of the 26-week RCT, participants in the experimental group will be asked to continue using the programme and participants in the control group will ‘cross-over’ to the StayFitLonger programme. This sub-study will last 22 weeks and indicators of adherence will be recorded throughout the entire duration of the StayFitLonger study (48 weeks). This will allow us to assess whether adherence is maintained over time and whether it is influenced by personal characteristics, the presence or not of supervision and the type of intervention. Usability, acceptability and user experience will also be evaluated.

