### Efficacy trial

#### Design

The design of the efficacy trial and adherence sub-study is illustrated in Table 1. The efficacy trial will be a double-blind parallel group multicentric RCT. It will be completed in three sites: Centre Leenaards de la mémoire – Centre hospitalier universitaire Vaudois (CHUV) in Switzerland; Institut universitaire de gériatrie de Montréal (IUGM) of the Centre intégré universitaire de santé et de services sociaux Centre-Sud-de-l’Île-de-Montréal (CIUSSS-CSMTL) in Canada; and Brusano and Centre Public d’Action Sociale (CPAS) of Woluwe-Saint-Lambert in Belgium. Participants will be randomised to one of two home-based computerised intervention conditions, the StayFitLonger training programme (experimental) or the comparator, an active control training programme. Outcome measures (Table 2) will be collected at two timepoints: pre-training (T0; within 6 weeks prior to the start of the intervention) and post-training (T1, within 4 weeks following the end of the 26-week training). Of note, a second exploratory post-training assessment (T2), not part of the RCT, will be performed within 4 weeks following the end of the adherence sub-study. At each timepoint, there will be two assessment visits. Within a month following the T0 assessment, introductory courses in groups of a maximum of six people will take place to introduce the features of the programme and describe the different physical and cognitive exercises. This will mark the beginning of the training that will take place at home for 26 weeks (see Table 1 for details). Participants will be supervised through home visits and monthly phone calls to monitor their use in relation to recommendation and address problems with the use of the programme.

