#### Randomisation and blinding procedure

A randomisation list will be generated in Switzerland, independently from the research project and implemented using REDCap. In each site, a team member not involved in assessment or monitoring will assign participants by pressing a “randomisation” button on REDCap. A stratification will be done according to the frailty status. Within each stratum (robust and pre-frail), participants will be assigned to one of the two conditions (StayFitLonger or active control) according to separate randomisation schedules with a 1:1 ratio. Couples (e.g., married individuals) who participate in the study will be assigned to one of the two conditions as a pair: the first member of the couple will be randomised, and the second will be assigned to the same intervention. This has been implemented to avoid contamination in cases where two individuals living in the same household would be randomized to different training programmes.

Assessors will be blind to the hypotheses and to participants’ assignment, as they will only have access to the testing sessions. Participants will be asked not to discuss their training programme with assessors. If such a circumstance were to occur, it will be reported but should have minimal effect on data integrity, as assessors will be blinded to the hypotheses. Research team members responsible for the statistical analyses will be blind to the training conditions. Study coordinators and instructors involved in the introductory courses and supervision of home-based training will not be blind. Participants will be aware that the trial has two different training conditions and that they will be randomly allocated to one of them. However, they will not be informed of the study hypotheses and therefore will not know which one is the experimental condition. Both programmes will have a similar main screen layout and name, and the wording of the recruitment documents and consent forms will not convey the notion that one condition is hypothesised as inferior in terms of its effects on physical capacities and cognition [48].

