##### Supervision during the intervention

Participants will receive a phone call and a home visit on week four and on week eight. Then, they will receive two phone calls (one from the physical activity instructor and one from the cognitive activity instructor) every four weeks. These will serve to identify and help participants to resolve difficulties with the programme, devices or exercises, and to obtain information about their health.

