### Adherence sub-study

#### Design

The adherence sub-study will be a pragmatic quasi-experimental study including all participants from the Swiss and Canadian sites (about 96). Following the 26-week efficacy trial, participants in the experimental group will be asked to continue to use the StayFitLonger programme with no supervision and will be invited to a refresher course to answer questions and discuss potential issues that occurred during the RCT. Participants in the control group will cross-over to use the experimental programme for 22 weeks (Table 1).

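### In the 22-week sub-study, the experimental group has a stated enquiry for falls but none for other adverse events, because those are tied to supervision contacts that have ended

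*Protocol article*

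**What the plan says.** The protocol article's Potential harms section gives two collection rules. Falls and their severity are asked about for the year before T0 and "in the T0-T1 and T1-T2 periods", so the fall question runs through the sub-study. For all other events, "participants will be asked to report and discuss any potential adverse event during home visits and phone calls". The section then lists a typology that is mostly not about falls, and says that all adverse events will be assessed and followed.

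The Design section of the efficacy trial says what the visits and calls are: "Participants will be supervised through home visits and monthly phone calls to monitor their use in relation to recommendation". The section on supervision during the intervention schedules them: "Participants will receive a phone call and a home visit on week four and on week eight", followed by two calls every four weeks. It gives learning about participants' health as one of their purposes.

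The Design section of the adherence sub-study then says that "participants in the experimental group will be asked to continue to use the StayFitLonger programme with no supervision". The only further contact it names for this group is a "refresher course to answer questions and discuss potential issues that occurred during the RCT".

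**The concern.** Each rule is reasonable alone, but together they leave a hole. Non-fall events are asked about at contacts that make up the supervision, and the experimental group loses that supervision at the end of the trial. The fall question was carried forward to T1-T2 and the general question was not.

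The sub-study is the phase closest to intended use: older adults, some of them pre-frail, doing strength and balance exercises at home without an instructor calling. Exacerbation of an existing illness, or worsening of symptoms present at T0, cannot be picked up by a fall question. Assessment of severity, expectedness and causality can start only once an event is known. If non-fall events appear less often after week 26, a reader could not tell a safer period from one in which nobody asked.

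**Working it through.** The article states no figure on this point, so there is none to reproduce. The check is a comparison of the text, followed by simple arithmetic for scale.

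**Comparison, experimental group**

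| | Weeks 1 to 26 (trial) | Following 22 weeks (sub-study) |
|---|---|---|
| Falls | Asked, T0-T1 | Asked, T1-T2 |
| Other adverse events | Asked at home visits and phone calls | No stated enquiry |
| Supervision contacts | Weeks 4 and 8, then calls every four weeks | None |
| Other named contact | Introductory sessions | Refresher course, looking back at the trial |
| Closing assessment | T1 | T2, with no general adverse-event question mentioned |

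The withdrawal of supervision is not loose wording. The Objectives section lists "the presence or not of supervision and the type of intervention" among the factors that may influence adherence, and the Discussion describes follow-up beyond the trial as unsupervised.

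**Scale**

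Inputs: 22-week sub-study and 48 weeks in total (Objectives and hypotheses); about 96 sub-study participants from the Swiss and Canadian sites (Adherence sub-study, Design); 1:1 allocation (Randomisation and blinding procedure); about 25% dropout (Sample size calculation).

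- Share of this arm's programme time: 22 / 48 = 45.8%, about 46%.
- Arm size, assuming an even split: 96 / 2 = 48.
- Person-weeks with full retention: 48 x 22 = 1056.
- Person-weeks if 25% are lost before the sub-study starts: 48 x 0.75 = 36 continuing; 36 x 22 = 792.

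The even split is an assumption. "A stratification will be done according to the frailty status", and no stratification by site is named, so the two sub-study sites need not divide exactly in half. The 46% share does not depend on the split. All these figures measure exposure time; none is an estimate of missed events.

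**Recall if asked at T2**

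T2 takes place within 4 weeks after the sub-study ends, so a question covering the sub-study looks back about 22 to 22 + 4 = 26 weeks.

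**The case against.** The strongest objection is that this is a journal article. It never says that visits and calls are the only route, and it never says that non-fall events go uncollected after T1. It refers to a full protocol that is not shown, and Table 1, the schedule of assessments, is missing from the text. Either could contain a further contact or a general question at T2. The harms section also undertakes to record and follow all adverse events, with no cut-off at T1. Participants still attend T2, and nothing stops them from volunteering a complaint.

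Much of this stands, and it limits the claim. A reader might infer that non-fall harms in this arm are not collected at all after T1. The article does not support that: what is missing is a stated enquiry, not every possibility of a report. What survives is more than silence in a condensed text. The article does state its harms rules, explicitly extends one of them to T1-T2, and ties the other to contacts that it withdraws elsewhere. The general undertaking about all adverse events does not say how such events would come to light in this arm.

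A reader might also extend the point to the control group after cross-over. The text does not say whether that group is supervised in the sub-study, so nothing can be concluded about it.

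Finally, the phase is exploratory and not randomised, and falls, the one harm that the article names at the outset, are covered. That argues for low priority and does not remove the gap.

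**Conclusion.** The point holds as a minor one. On the rules as the article gives them, the experimental group has solicited falls but no stated solicitation of other adverse events for 22 of its 48 weeks. That is about 46% of its StayFitLonger time: some 1056 person-weeks if 48 participants continue without loss, or 792 if a quarter have dropped out by then.

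This rests on reading the visits and calls in the harms section as the supervision contacts described elsewhere, and on there being no other contact in Table 1 or the full protocol. If there is one, saying so in the text settles the matter.

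The effect is confined to safety ascertainment in the sub-study. A reader might infer that the efficacy result or the comparison of harms to week 26 is compromised. It is not, because both groups have the same stated enquiries during the trial.

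**What to change.** At the existing T2 visit, ask all sub-study participants about the full adverse-event typology for T1-T2, alongside the fall question. An unblinded study coordinator should ask it after outcome testing is finished, so that assessors stay blind. Asking both groups keeps ascertainment the same whatever supervision the cross-over group receives. In the report, show adverse events separately for supervised and unsupervised periods, and state how non-fall events were obtained in each.

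The cost is a few minutes at a visit that already takes place. The drawback is recall over about 22 to 26 weeks, which the plan already accepts for falls.

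For participants who have already had their T2 visit, the gap can only be reported. Having completed 48 weeks is not the same as being past T2, since that visit may come up to 4 weeks after the sub-study ends. Whether someone can still be asked should therefore be decided from the actual date of the T2 visit.

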### Access to data

All site coordinators and principal investigators will be given access to the cleaned data sets. They will have direct access to their own site’s data sets, and will have access to other sites data by request. To ensure confidentiality, data dispersed to research team members will be blinded of any identifying participant information.

### Dissemination of study results

Study results will be published in international journals with peer-reviewed committees. They will also be presented to the research community in national and international conferences and to the public through lay audience talks and press releases. Interim analyses will be conducted once a site has completed the RCT as required by one of the funding organization (the Active and Assisted Living Programme).

## Trial status

Protocol CER-VD 2018–01898 version number 2, December 2018. Recruitment began in January 2019 in Switzerland and Canada and in January 2020 in Belgium. Recruitment was on hold between March and July 2020 in Belgium due to COVID-19. As of August 7, 2020, recruitment has been completed in Canada and Switzerland and has resumed in Belgium. Date of recruitment completion is anticipated to be October 2020.

## Discussion

This study will measure the effect of the StayFitLonger programme, a computerised home-based training, which combines physical and cognitive activities and includes elements to favour social life as well as feedback and instructions from a virtual coach to enhance motivation and adherence. The overarching objectives of the study are: 1) to provide scientific evidence that such a programme can promote physical and cognitive health while staying at home; 2) to examine the level and determinants of adherence to a home-based computerised programme as well as assessing participants’ perception of the programme and its functionalities.

The StayFitLonger programme includes several innovative features. First, while most physical activity interventions designed for older adults rely on aerobic training, the StayFitLonger programme focuses on balance and strength and was originally designed for older adults at risk of falling. Encouraging pilot results (T&E study, unpublished data) indicated an improvement in balance after 6 months compared to home-based exercise programme. Therefore, we believe that this approach could be beneficial to older adults at risk of frailty and that it could improve strength and reduce falls. The inclusion of pre-frail and robust participants will offer the opportunity to assess the impact and relevance of the programme for older adults with a range of physical capabilities. If necessary, there will be an opportunity to adjust the content in terms of difficulty so that it can broaden the targeted population of the programme for future use or studies. Another innovation is the use of motion sensors during physical exercises and as an outcome, which will provide precise and objective measurements on mobility for a better characterisation of how participants complete the exercises and on physical improvements.

Although the StayFitLonger intervention focuses on cognitive and physical training, it includes complementary approaches that could potentiate its effect, in particular the possibility for participants to interact with other players, promoting an active social life [42], and the inclusion of psychoeducational content. In addition, the virtual coach will provide some elements of feedback and reward, which is expected to increase motivation and adherence [43]. This is innovative, as participants in home-based training benefit from limited training assistance and coaching and this negatively impacts use over the long-term.

One important aspect of the study is to provide a direct measure of adherence, and to follow participants beyond the RCT, which will provide adherence data under unsupervised and more pragmatic conditions. To our knowledge there is no consensus on a method to assess adherence and therefore many different approaches are used in the literature with varying limitations [81]. Precise measurement of adherence to a home-based exercise programme is limited by the need to rely on self-reported measures. However, the use of a computer programme makes it possible to measure the use of the tablet and different exercises to the minute. This will provide a rich set of accurate data on dose, volume and frequency of training.

While the efficacy of a computerised training programme is essential, one prerequisite to its use by the population is that the programme is easy to use and matches the needs of older adults.

The StayFitLonger study will provide critical information on usability, acceptability and user experience, which are inter-related concepts providing insights on the potential long-term use of a technology [36, 37]. Usability refers to the ease of use of a technology and is characterized as a person’s perception of its efficacy, efficiency and satisfaction [82]. Acceptability is an a priori willingness to use a tool, while acceptance is an a posteriori pragmatic evaluation of a tool after its use [83]. They are known to be influenced by usability but also by other factors, such as perceived usefulness by the user and others, and this is particularly true among seniors [82]. User experience, which refers to a person’s perceptions and responses that result from the technology use and/or anticipated use is also dependant on usability and has an impact on acceptability [84]. Results obtained on these parameters are important to determine the factors that influence future use, but they can also help improving the application or designing new solutions to provide the best experience for end users.

The design includes an active control training as a comparator that mirrors the structure of the StayFitLonger training. Using an active control condition will allow us to attribute the improvement to the particular content and format of the StayFitLonger programme. Relying on an active control condition as a comparator is a methodological strength compared to other studies that used a no-contact or wait-list control condition. However, this comes with additional challenges in terms of design and power. One of these challenges is that we need to ensure that participants in each group have the same expectation regarding the capacity of their assigned training to yield improvement [48]. To control for this effect, we included an expectation scale and will assess whether it differs among groups and whether expectations are related to pre-post changes.

We are aware of the potential limitations associated with this study. First, the StayFitLonger study spans over a full year and it is hard to predict whether participants will commit for such an extended period of time. Note, however, that we rely on a two-part design, with the RCT portion only lasting 26 weeks, and that attrition will be examined separately for the two portions. Second, while the use of feedback and rewards in the programme was meant to boost motivation, the frequency at which they appear has been set as a fixed parameter to avoid a bias between participants. Hence, this aspect was not personalized. In order to take into account that some participants may dislike receiving regular feedback, they will be able to deactivate this feature during the adherence sub-study. Adherence will be measured from the tablet application, but it is possible that some participants, intentionally or not, start an activity and let the application run in the background while they are actually not doing the activity. To counteract this possibility, the StayFitLonger programme includes a function that stops the application after 10 min of inactivity. However, it has not been implemented in the active control programme. This will be monitored as carefully as possible during data analysis to assess possible outliers in the time of use data of the active control group.

In conclusion, the StayFitLonger study will examine the efficacy, adherence and perception of a home-based computerised multi-modal training programme in robust and pre-frail older adults. Positive results on the StayFitLonger study will pave the way to further development and commercialisation of a scientifically grounded and empirically validated application which will improve the physical and cognitive health associated with independent life at home.

